## Publications

The preparation and submittal for publication of manuscripts containing the study results shall be in accordance with a process determined by mutual written agreement among the study’s investigators.

Appendix 1: Data and Safety Monitoring Plan

Procedures for implementing a Data Safety and Monitoring Plan (DSMP) at the University of California San Francisco have been developed on a campus-wide basis in conjunction with the Institutional Review Board (Committee on Human Research), the Office of the Vice-Chancellor for Research and the Office of Clinical Research in the School of Medicine. The Data and Safety Monitoring Plan for the proposed project incorporates the policies on human subject data and safety monitoring specified by the UCSF Committee on Human Research (i.e. UCSF Institutional Review Board).

# 1.  Risk Assessment - Minimal Risk

This study represents a minimal risk intervention. In this study, we will recruit 90 participants who are current smokers who have an intention to quit smoking within 6 months and who are homeless into a pilot randomized controlled trial of a contingency management (CM) smoking cessation intervention (see Research Strategy section). In this trial we will assess feasibility and acceptability of the study protocol, including CM for smoking cessation, escalating incentives, and study procedures for recruitment and retention. This study will provide preliminary data and inform development for the subsequent full-scale RCT to test the efficacy of the CM intervention for long-term absitnence. Participants will receive escalating incentive payments for demonstrating biochemically-verified smoking abstinence. The proposed study will be conducted by study staff in a private room at the Tom Waddell Urban Health Clinic (Aim 2). Staff will be well-trained in the program components. All data will be stored in a password protected database, on a secure UCSF server. The inclusion criteria do not allow individuals at very high risk for adverse events to be enrolled (e.g., recent myocardial infarction, or pregnancy). Participants will be required to attend usual smoking cessation care at the Tom Waddell Urban Health Clinic, which involves weekly one-on-one counseling conducted by behavioral counselors and receipt of nicotine replacement therapy (NRT) (the primary cessation medication in the clinical trial) dispensed on-site by a pharmacist and covered by participants’ health insurance. The study will provide a 12-week supply of NRT to participants who are unable to get covered medications due to insurance-related barriers. Pharmacists will determine dosage of NRT based on articipants’ current consumption level and nicotine dependence, and will assess whether the dose is meeting their needs. Primary care providers (PCPs) will verify and document in the EHR that there are no contraindications to receiving NRT such as having had a myocardial infarction in the 2 weeks prior to enrollment or pregnancy. HIPAA-trained study staff will access the EHR weekly to verify participants’ attendance of counseling and receipt of NRT. We anticipate that some participants may be co-prescribed varenicline or bupropion with NRT; we will document receipt of non-NRT medications by self-report at each visit and verify this information through the EHR. To decrease the likelihood of an adverse event during the study, study staff will provide information on the medications, directions of  use, indications of use, side effects of medications at the enrollment visit. At each assessment visit, study staff will assess adherence to medication and side effects of medications. Participants will also be asked to call study staff in between visits if new symptoms were to arise.

# 2.  Description of Adverse Event Grading and Anticipated Adverse Events

In this study, we do not anticipate moderate or severe adverse events (AE).  AE will be scored as follows:

1. = No adverse event or within normal limits
2. = Mild AE – not requiring follow-up
3. = Moderate AE – resolved with follow-up
4. = Severe AE – resulted in inability to carry on normal activities and required professional medical attention, requiring hospitalization
5. = Life-threatening or disabling AE – results in an immediate risk of death and/or results in persistent or significant disability
6. = Fatal AE

We anticipate at most mild AE, including potential adverse effects of nicotine withdrawal or hunger among those reducing consumption or quitting cigarette smoking. Risks of participating in one-on-one counseling sessions and assessment interviews include fatigue from answering questions, worry about loss of confidentiality/privacy, and perception of coercion to participate. The Principal Investigator (PI), [name], in consultation with the research team, is responsible for evaluating each AE and for determining whether the AE affects the risk/benefit ratio of the study and whether modifications to the protocol and consent form are required.

Participants will attend abstinence assessment visits according to the following schedule: daily visits for the 1^st^week, twice weekly for the next 3 weeks (1 month), once weekly for the next 8 weeks (3 months), and monthly until the one-year follow-up (1 year). In addition, participants will be required to attend cessation services at the TWUHC that include behavioral counseling and pharmacotherapy. At each visit, we will ask participants whether they had experienced any adverse effects since the last visit. Participants will also be encouraged to call the study team in between visits if they were to occur.  Adverse events will be graded according to their significance for severe consequences, such as injury or death.

1. Examples of severe adverse events (life-threatening or disabling and requiring medical attention).  Severe adverse events that may occur during the CM intervention include death and cardiovascular events, though these are extremely rare in the absence of significant cardiac pathology. Other serious adverse events include suicidal ideation and/or self-injurious behaviors. For these adverse events, participants will be referred to the nearest emergency room.
2. Examples of moderate adverse events (resolve with treatment).  Moderate adverse events include any new psychiatric symptoms or side effects related to the use of cessation medications (e.g. nightmares for NRT, seizures for bupropion, new depressive symptoms for varenicline). For these events, we will refer the participants to their primary care providers.
3. Examples of mild adverse events (ones that do not require treatment).  Mild adverse effects may be symptoms of irritability or fatigue or hunger from stopping smoking. Participants will be offered information on these symptoms prior to the onset of the study and during the study. Participants will be given a list of resources, including food pantries, and other locations that offer free food.

# 3.  Description of Monitoring Study Progress and Safety of Human Subject Participants

The PI has primary responsibility for the overall conduct of the study and for the safety of participants. The PI will ensure that (1) the informed consent process is conducted appropriately and that informed consent is obtained prior to proceeding with any study procedures; (2) only eligible subjects, per protocol eligibility criteria, are enrolled in the study; (3) data are collected and analyzed per protocol requirements; (4) procedures are implemented to ensure that the project is consistently monitored for possible adverse events; (5) adverse events are reviewed promptly and reported as required to the UCSF Committee on Human Research (i.e. UCSF Institutional Review Board); (6) the privacy and confidentiality of study subjects is maintained.  While implementation of aspects of the DSMP may be delegated to members of the research team, the PI maintains ultimate responsibility for the project and for the safety of study participants.

The co-investigators, [name], and [name], along with the statistician [name], and other research team members (TBD, study staff) will participate in the monitoring of the safety of study participants together with the PI.  Every six months, the PI, the statistician, and study staff will prepare a written report on the progress of the project including data on: enrollments, comparison of target to actual enrollment, overall status of the study participants, information on race/ethnicity, age and gender, adverse events, and serious adverse events. The PI and the research team will meet to review information contained in the reports.  During the reviews, the PI and research team will determine whether additional effort is required to foster the progress of the study, whether adverse events have occurred, whether adverse events were dealt with appropriately, and whether adverse events were corrected and immediately reported to the UCSF Committee on Human Research. The PI and team will determine whether the study should be continued, terminated, or modified based on observed beneficial or adverse effects.

# 4.  Plans for Assuring Compliance with Requirements Regarding the Reporting of Adverse Events

The PI is responsible for reporting adverse events to the research team and to the UCSF Committee on Human Research. Mild and moderate adverse events will be reported within 10 working days of the occurrence. Severe, life-threatening or fatal adverse events will be reported immediately to the PI, who will notify the UCSF Committee on Human Research (CHR) within 24 hours by telephone. An expedited report will follow within 10 days. Specifically, the following will be reported, in writing: 1) all severe adverse events associated with the study procedures, and/or 2) any incidents or problems involving the conduct of the study or patient participation, including problems with the recruitment and/or consent processes and/or education of participants about safety. The PI will provide a written report of moderate adverse events during the course of the study to the CHR on an annual basis.

When the PI receives a report of a severe or greater adverse event, she will immediately notify all members of the research team.  A meeting will be held within ten days to discuss whether study procedures should be modified.  Moderate and mild adverse events will be tabulated by the PI and study staff, who will produce reports of adverse events every six months. The research team will review reports to identify any potential trends. If trends are noted, preventive measures will be implemented, such as changing the education of participants in the study to emphasize prevention of the adverse event. This means that study staff have been trained to recognize, respond to, and record adverse events when they occur or immediately after they occur to insure the safety of the human subjects; and to report adverse events to the PI in a timely manner to ensure compliance with institutional policies on human subject protection. This also means that study staff engaged in data collection can contact the PI as soon as an adverse event occurs.

Cardiac events or deaths are very rare in persons engaging in smoking cessation interventions. We will stop the study based on instructions from the UCSF CHR, which will be notified immediately if a participant in this study experiences a severe adverse event while enrolled in the study. Because the proposed study entails minimal risk, we do not anticipate that a DSMB will be required.  However, if the funding agency requests a DSMB, we will work with them to form one.

1. Informed consent must be obtained prior to any study-specific procedures and may be obtained prior to the screening window.

   ^2^ Participants will be asked to provide an expired carbon monoxide sample at each abstinence assessment visit, and complete a short questionnaire. At 2 weeks, 1 months, 3 months, 6 months and 1 year follow-up, participants will also be required to complete a longer questionnaire.

   ^3^ Between 6 months and 1 year follow-up, participants will be asked to check in by telephone monthly. [↑](#footnote-ref-2)

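### Appendix 1 triggers 24-hour review-board notice by severity grade alone, without reference to the Section 8.2 serious-event definition, and lists bupropion seizures as moderate

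*Protocol*

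**What the plan says.** Section 8.2 of the protocol defines a serious adverse event by outcome, in seven criteria, and attaches no reporting time. Section 8.3.1 requires grading by CTCAE. Section 8.6 gives no time either; it defers to institutional and regulatory requirements.

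The numeric times are in Appendix 1 section 4. For lower grades, "Mild and moderate adverse events will be reported within 10 working days of the occurrence"; the sentence names no recipient. For higher grades, "Severe, life-threatening or fatal adverse events will be reported immediately to the PI", who then telephones the review board within 24 hours. The team notification and meeting that follow are also set off by grade: "When the PI receives a report of a severe or greater adverse event". The closing paragraph of the same section, on stopping the study, promises the review board immediate notice of a severe event. Moderate events also have a periodic report: "The PI will provide a written report of moderate adverse events during the course of the study to the CHR on an annual basis".

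The grades come from a scale in Appendix 1 section 2, which is separate from CTCAE. In that section the moderate examples include "nightmares for NRT, seizures for bupropion, new depressive symptoms for varenicline", to be handled by referral to the primary care provider. Section 5.5.1 allows bupropion, and Section 1.4 expects some participants to be prescribed it alongside NRT.

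**The concern.** Severity and seriousness are different properties. Severity describes how intense an event is. Seriousness, as Section 8.2 uses it, describes what the event led to or could lead to. Expedited reporting normally follows seriousness. Here it follows severity, and the section that sets the times does not mention Section 8.2. An event can therefore meet the protocol's own definition of serious and still be placed, by a stated rule, on the slower clock.

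The seizure example makes this practical. Staff reading Appendix 1 find a drug-related seizure listed beside nightmares as moderate, and nothing at that point asks whether the event also meets Section 8.2. What is at stake is the timing of review-board notice for a narrow class of events, including the immediate notice linked to stopping the study.

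**Working it through.** No sample size, power or event count is involved. The check is a comparison of text, followed by a short calendar calculation.

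**Step 1. Match the Section 8.2 criteria to the Appendix 1 levels that set off the 24-hour notice** (severe; life-threatening or disabling; fatal).

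| Section 8.2 criterion | Matching level on the Appendix 1 scale |
| --- | --- |
| Death | Fatal |
| Life-threatening | Life-threatening or disabling |
| Hospitalization | Severe |
| Persistent or significant disability | Life-threatening or disabling |
| Birth defect, or cancer | None |
| May need intervention to prevent a listed outcome | None |
| Changes the study's risk/benefit ratio | None |

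Four of seven criteria have a matching level. Of the other three, the risk/benefit criterion is largely met another way, because Appendix 1 section 2 has the PI evaluate every event for that effect. Birth defect is remote, because pregnancy is an exclusion (Section 4.1.2). Two kinds of event remain with no trigger of their own: an event that may need intervention to prevent a listed outcome, and a cancer. Either still takes the fast route if it is also graded severe or worse. The count is of criteria, not of events that would be missed.

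**Step 2. Follow the seizure example.** A seizure that leads to admission meets the severe wording and gets the 24-hour notice, despite being listed as moderate. A seizure treated without admission is moderate by the stated example. Whether it also meets Section 8.2 is a case-by-case judgement under the intervention criterion. If it is judged to meet it, and if the Appendix 1 scale sets the grade, the 10-working-day clock applies.

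**Step 3. Size the difference in notice.** Assumptions: the 10-working-day report goes to the review board, the working week is Monday to Friday, and there are no holidays.

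- Event on a weekday: the tenth working day is 14 calendar days later.
- Event on a Saturday: 13 calendar days later.
- Event on a Sunday: 12 calendar days later.

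Subtracting the 1 day allowed on the fast route gives 14 − 1 = 13, 13 − 1 = 12 and 12 − 1 = 11. The difference is at most 11 to 13 days. The lower limit is 0, if institutional rules under Section 8.6, or the duty in Appendix 1 section 3 to report as required, bring notice within 24 hours.

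**The case against.** The other side has a good case. No text says that a seizure treated without admission is serious; Section 8.2 leaves that to judgement. If CTCAE governs, as Section 8.3.1 requires, the Appendix 1 example does not fix the grade, and the slow route does not follow. Appendix 1 also has routes with no severity threshold. Section 3 makes the PI responsible for prompt review of events and for reporting them as required, and has the team check that events were reported to the review board at once. Section 4 calls for written reports of "any incidents or problems involving the conduct of the study or patient participation". Under the severe examples, section 2 describes suicidal ideation and self-injury as serious events, which suggests the authors meant the fast route for serious events generally. The tested intervention is an incentive payment, and bupropion is prescribed by participants' own providers.

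All of this stands as a limit on the size of the point. It does not remove the point. None of these routes gives a stated time for a serious event graded below severe. Loose use of the two words, and two grading scales with no statement of which governs, leave staff to guess which clock applies.

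Three stronger readings are tempting but unsupported:

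- A reader might infer that serious events in general miss the fast route. They do not, because the grades capture the four main outcomes.
- A reader might infer from the annual report that the review board could wait up to a year to hear of a moderate event. Section 4 opens by making the PI responsible for reporting to both the research team and the review board. The 10-working-day sentence is therefore more naturally read as covering the board, with the annual report as an additional summary.
- A reader might infer delayed care, or that the study could not be stopped. The PI is on call at all times (Section 1.4), "study staff engaged in data collection can contact the PI as soon as an adverse event occurs", and the team's review in Appendix 1 section 3 can modify or terminate the study.

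**Conclusion.** The point holds, and it is minor. The 24-hour and immediate notices depend on severity grade and make no reference to Section 8.2. Two kinds of serious event therefore lack a trigger of their own, and the seizure example steers one plausible case to the slower clock. The consequence is a possible difference in review-board notice of between 0 and about 11 to 13 days. The upper figure requires that the Appendix 1 scale governs, that the event is judged to meet Section 8.2 without being graded severe, and that no institutional rule acts sooner. The documents show no delay in care. Sample size and the descriptive feasibility analysis are unaffected.

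**What to change.** Make three changes of wording:

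1. In Appendix 1 section 4, including its closing paragraph on stopping the study, apply the 24-hour notice to any event that meets Section 8.2 as well as to any event graded severe or worse.
2. In Appendix 1 section 2, remove seizures from the moderate examples, or state that each seizure is graded case by case and checked against Section 8.2.
3. State whether CTCAE or the Appendix 1 scale sets the grade used for reporting.

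Two clerical corrections could go in at the same time. Name the recipient of the 10-working-day report. Align the heading over the severe examples, which describes them as life-threatening or disabling, with the scale above it, where that is a separate and higher level.

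The cost is one added field on the adverse event form (meets Section 8.2: yes or no) and a few more expedited reports. No new assessments are needed.
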